#### **7.5.4 Routine laboratory parameters and urinalysis**

A pregnancy test will be performed by analysis of a urine sample for Human Chorionic Gonadotrophin (HCG) collected from female participants at screening, the day of each immunisation and at the final visit. The analysis will be conducted by a member of the study team according to trial-specific standardised operating procedures.

Peripheral blood and urine will be collected and analysed, as described in **section 7.2.3**, for the following parameters at the time points specified in **Appendix 2**, and at additional time points if indicated to further evaluate or follow up adverse events:

##### **7.5.4.1 Blood**

- Creatinine, ALT, total and direct bilirubin, glucose
- Hb, total WCC, neutrophils, lymphocytes, platelets
- Troponin I will be performed 14 days post MVA / saline vaccinations (Visits 12 and 15) if there is clinical evidence for cardiologic disease or as indicated by the clinical investigator.

##### **7.5.4.2 Urine**

- protein, blood

#### **7.5.5 Solicited local and systemic clinical and laboratory adverse events**

Various local and systemic adverse events are known to be associated with licensed vaccines, and are referred to as '**solicited adverse events**'. These include disturbances in routine laboratory parameters, and are described in **Table 2** below.

Information on solicited adverse events will be collected at the clinics before and 30 minutes after each immunisation through direct questions asked during a structured face to face interview and through examination. This information will be recorded directly into the CRF. Participants will also be asked to complete a diary card (**Appendix 6**) recording solicited adverse events that start within 7 days of each immunisation, regardless of the route of immunisation they receive. Diary cards will be reviewed and discussed later at the scheduled 2 weeks follow-up visit after each immunisation, when the clinician will also enter solicited adverse event data onto the CRF. Diary card entries (e.g. severity grade of symptoms) might

be revised after discussion between the participant and the clinician. Any alterations should be dated and initialled by the study clinician directly onto the diary card. Where there is a discrepancy for the grade assigned on the same day as the visit, it is assumed that the grade assigned by the clinician is more accurate. Any discrepant report between the diary card and the CRF entry will be foot noted in the study report and analysis tables

All participants will be asked to contact the study site in the case of adverse events of suspected grade 2 or more for evaluation within the 7 days post immunisation period. A decision to offer the volunteer a visit to the clinic should be made and documented in the source documents. All participants with suspected grade 3 or more events should be seen by the study physician for further evaluations and confirmation of the reported grade.

In addition, systemic laboratory adverse events will be collected through routine laboratory testing according to the schedule (**Appendix 2**). These will be recorded on the standard laboratory reports and may be transcribed into the CRF or a copy of the laboratory report attached to the CRF.

**Table 2 Solicited adverse events**

| Type                             | Event                                                                                                                                                         |
|----------------------------------|---------------------------------------------------------------------------------------------------------------------------------------------------------------|
| Local AEs
(immunisation site) | Local Pain
Local Itching
Warmth
Redness in cm
Swelling (soft) in cm
Induration (hard) in cm
Blisters (blood or clear) in cm
Papule in cm |
| Systemic
Clinical AEs         | Temperature
Chills
Myalgia/flu-like general muscle aches
Aching joints
Malaise (excess fatigue)
Headache
Nausea
Vomiting                 |
| Systemic
Laboratory AEs       | Creatinine, ALT, total and direct bilirubin, glucose
Hb, total WBC, neutrophils, lymphocytes, platelets                                                    |

The events will be **graded** according to the toxicity table in **Appendix 8**.

**Relationship** will be recorded in the immunisation CRF but not on the diary card, on the assumption that any of these events starting within 7 days of an immunisation are at least possibly related. If the onset of the event is beyond 7 days, the event will be recorded on the adverse event CRF and a relationship determined by the investigator reviewing the event.

#### **7.5.6 Procedure for follow-up of adverse events and pregnancy**

The Investigator will make every effort to monitor all adverse events, regardless of severity, until resolution or stabilisation and to obtain documentary evidence of the outcome of pregnancy, in order to report this on the CRF during the trial. For volunteers who become pregnant before completing the vaccine series, no further immunisations will be given. A positive urinary pregnancy test result will be communicated to the participant as well as her ineligibility to continue with the immunisation schedule. Pregnant participants will be referred

to the Obstetrics and Gynaecology Department for the Mbeya Referral Hospital, MNH for further management and care. In Maputo, pregnancies occurring during the course of the study will be followed by obstetricians (study doctors) at the youth clinic at HCM, until delivery. The participant will be followed for all the remaining scheduled visits according to the schedule of procedures for safety evaluation. The maternal follow up during pregnancy, labour, delivery and post-delivery periods as well as the infant outcome will be documented in a Pregnancy Report CRF at various time points. Female participants will be required to use an effective contraceptive method until 3 months after the last vaccination, which is Visit 17. At this point the last pregnancy test will be performed according to the study flow schedule. After the database is locked and the trial is closed, any additional information about adverse events or pregnancy that comes to the attention of the investigator should be reported by email to the TMG and the Chief Investigator on behalf of the Sponsor. The study site will have available, free of charge, a variety of contraceptive methods (male and female condoms, oral and injectable contraceptives, etc). Counseling to prevent pregnancy and to use contraception will be performed on all study visits.

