### 4.1 Participant inclusion criteria

1. Age: 18 to 40 years
2. Willing to undergo counselling and HIV testing
3. Have a negative antigen/antibody ELISA for HIV infection
4. Able to give informed consent
5. Basic abilities to read and write
6. Satisfactory completion of an assessment of understanding prior to enrolment defined as 90% correct answers after three opportunities to take test
7. Resident in Dar es Salaam, Mbeya or Maputo catchment areas, and willing to remain so for the duration of the study
8. At low risk of HIV infection, defined as the absence of an identifiable risk factor/behaviour according to a risk assessment questionnaire. The following criteria will be considered high risk leading to exclusion:
  - sexual partner with HIV
  - sexual partner with unknown HIV serostatus who is also unwilling to use protective condoms consistently in all sexual relations
  - sexual partner is known to be at high risk for HIV
  - more than two sexual partners in the last 6 months
  - history of being an alcoholic [as medically defined or more than 35 units /week] or intravenous drug abuse or ongoing other chronic drug abuse (e.g. marijuana)
  - history of STI within past 6 months
9. Verbal assurances that adequate birth control measures are used not to conceive/father a child during the study and up to 3 months after the last vaccine injection. Adequate birth control is defined as follows:
  - Contraceptive medications delivered orally, intramuscularly, vaginally, or implanted underneath the skin
  - Surgical methods (hysterectomy or bilateral tubal ligation)
  - Condoms, diaphragms
  - Intrauterine device (IUD)
  - Abstinence
10. Women shall have a negative urinary pregnancy test
11. Be willing to practice safe sex for the duration of the study to avoid sexually transmitted infections including HIV

12. Good health as determined by medical history, physical examination, clinical judgment and by key laboratory parameters as judged by the study physician
13. Laboratory criteria within 8 weeks prior to enrollment:
  - Hb >10.5 g/dl
  - White blood cell count >2000 to <13,000 cells/mm^3
  - Neutrophils >1,100 cells /mm^3
  - Lymphocytes >1.0 cells/mm^3
  - Platelets >125,000/ mm^3
  - Random Blood Glucose <6.44 mmol/L; if elevated, then a Fasting Blood Glucose <6.11 mmol/l
  - Bilirubin <1.1 x uln
  - ALT <1.25 x uln
  - Creatinine <1.1 x uln

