#### 7.1.2 Visit windows

Immunisation visits are compliant with the protocol if they comply with the following target dates and visit windows:

DNA I (Visit 3, week 0): Day 0

DNA II (Visit 5, week 4): 28 days (+/-3) post DNA I

DNA III (Visit 8, week 12): 84 days (+/- 7) post DNA I

MVA I +/- CN54rgp140/GLA-AF (Visit 11, week 24): 84 days (+/-7) post DNA III

MVA II +/- CN54rgp140/GLA-AF (Visit 14, week 40): 112 days (+/-14) post MVA I +/- CN54rgp140/GLA-AF

If there is a delay >4 weeks, a decision will be made by the TMG as to whether immunisation will continue.

Safety follow up visits performed 14 days (2 weeks) after each immunization (Visits 4, 6, 9, 12 and 15) will be compliant with the protocol if they take place -3 to +3 days of the target date.

Safety follow up visits performed 28 days (4 weeks) after each immunization (Visits 7, 10, 13, 16) will be compliant with the protocol if they take place -5 to +5 days of the target date.

Long term immunogenicity and safety follow up visits are performed 84 days (12 weeks) and optional 168 days (24 weeks) after the last immunization and will be compliant with the protocol if they take place -14 to +14 days of the target date.

The primary endpoint and follow-up visits are scheduled for 2 and 4 weeks after the second MVA immunisation or at week 42 if immunisations have been discontinued will be compliant with the protocol if they take place  $\pm 7$  days either side of the target date respectively.

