### 7.3.4 Pregnancy test

Pregnancy tests will be performed from urine during screening, at each vaccination day and 3 months after the last vaccination visit (study Visit 17). Urinary pregnancy test results at

immunisation days will be available before vaccine administration. Positive pregnancy results after enrolment will not be reported as an adverse event but in a Pregnancy Report CRF. Pregnant women will be excluded from the immunisation schedule but continued to be followed-up for safety assessments.

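### Sections 7.5.6 and 7.3.4 treat Visit 17 as the 3-month point after the last vaccination, but the Visit 17 window (days 70 to 98) lets it fall before 3 months, and the sections disagree on which pregnancy test is last

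*Protocol*

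**What the plan says.** Section 7.5.6 sets the end of the contraception requirement for women and names a visit for it: "Female participants will be required to use an effective contraceptive method until 3 months after the last vaccination, which is Visit 17". Its next sentence puts the final pregnancy test there: "At this point the last pregnancy test will be performed according to the study flow schedule". Section 7.3.4 makes the same equation, placing the post-vaccination test "3 months after the last vaccination visit (study Visit 17").

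The visit timing is fixed elsewhere. Section 7.1.2: "Long term immunogenicity and safety follow up visits are performed 84 days (12 weeks) and optional 168 days (24 weeks) after the last immunization", with compliance allowed from 14 days before to 14 days after the target. Appendix 1 gives the same target and window for Visit 17, counted from Visit 14.

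Other sections state the duty without naming a visit. Inclusion criterion 9 in section 4.1 asks for birth control "during the study and up to 3 months after the last vaccine injection". Sections 2.4.2 and 4.4 also give 3 months and tie it to no visit.

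On the last pregnancy test, section 7.5.4 has urine "collected from female participants at screening, the day of each immunisation and at the final visit", and Appendix 2 marks a test at both Visit 17 and Visit 18. Section 7.7 lets the final visit be Visit 17 or, optionally, Visit 18.

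**The concern.** The protocol uses one event, Visit 17, to mark the end of a period that it defines separately by elapsed time. The two agree only if the visit cannot fall before the period is over, and the visit window does not ensure that.

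Section 2.4.2 gives the purpose of the period as limiting risk to an unborn child. If site staff use Visit 17 as the marker, a woman seen early in the window could be told that the requirement has ended while she is still inside it. If no Visit 18 follows, a conception between that visit and the 3-month point has no later scheduled test to detect it. Pregnancy is an expedited-reporting event (section 8.2) with its own report form and maternal and infant follow-up (section 7.5.6), so a missed case would be a gap in safety data that the protocol sets out to collect.

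**Working it through.** **Inputs**

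- Last scheduled vaccination: Visit 14, day 280 (Appendix 1).
- Visit 17: 84 days after Visit 14, window plus or minus 14 days (section 7.1.2, Appendix 1).
- Visit 18: 168 days after Visit 14, window plus or minus 14 days, optional (section 7.1.2, Appendix 1).
- Length of 3 months: not defined in days. This is an assumption, taken here as 12 weeks (84 days) or as three calendar months, which run from 89 to 92 days depending on the starting date.

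**Reproducing the protocol's own figures**

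- Visit 17 target: 280 + 84 = day 364, and 364 / 7 = week 52. This matches Appendix 1.
- Visit 18 target: 280 + 168 = day 448, and 448 / 7 = week 64. This also matches.

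**Window, in days after the last vaccination**

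- Earliest compliant Visit 17: 84 - 14 = 70.
- Latest compliant Visit 17: 84 + 14 = 98.

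**Shortfall = length of 3 months minus day of Visit 17** (a negative value means that the visit is after the 3-month point)

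| Reading of 3 months | Earliest (day 70) | Target (day 84) | Latest (day 98) |
|---|---|---|---|
| 12 weeks, 84 days | 14 | 0 | -14 |
| Shortest calendar, 89 days | 19 | 5 | -9 |
| Longest calendar, 92 days | 22 | 8 | -6 |

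On every reading the earliest compliant Visit 17 is before 3 months and the latest is after it. The target is on time on the 12-week reading and about a week early on the calendar reading.

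**Which test is last**

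- Visit 18 not held: the final visit is Visit 17 (section 7.7), so sections 7.5.4 and 7.5.6 agree. No scheduled test follows Visit 17, and it may fall before 3 months.
- Visit 18 held: section 7.5.6 puts the last test at Visit 17, section 7.5.4 puts it at the final visit, now Visit 18, and Appendix 2 has a test at both. The sections conflict, but a test does take place 168 - 14 = 154 to 168 + 14 = 182 days after the last vaccination, past 3 months on any reading.

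The timing gap and the conflict over the last test therefore arise in different situations.

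**The case against.** A reader might infer that the protocol ends contraception up to three weeks early. The documents do not support that. Nothing expressly releases a participant at Visit 17. The duty is stated as 3 months in section 2.4.2, criterion 9 of section 4.1, section 4.4 and section 7.5.6 itself, and criterion 9 also covers the time on study. Section 7.5.6 requires counselling on contraception at all study visits, which includes Visit 17. The reference to the visit is an added description of the 3-month point, and three weeks is the extreme of the window under one reading of an undefined unit. On the protocol's own usage, which equates 3 months with a visit at 12 weeks, the target is exactly on time.

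It might also be inferred that all of the at least 50 women planned in section 1.1 are affected. That figure counts women under the rule. The testing gap needs an early Visit 17 and no Visit 18. Although optional, Visit 18 appears to be the usual course: section 7.1 expects long-term visits to run to 24 weeks, section 1.1.5 gives a total duration of 64 weeks, and Appendix 2 treats the large Visit 17 blood draw as the fallback when Visit 18 is unlikely. Nor would every later pregnancy go unrecorded, since section 7.5.6 asks for pregnancy information that reaches the investigator after database lock to be reported, though that depends on someone coming forward.

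All of this stands, and it makes the point small. It does not remove the point. Visit 17 is the only scheduled visit that the protocol offers as a marker for the end of the period, two sections use it that way, and no reading of 3 months makes the earliest compliant visit late enough. The during-the-study wording of criterion 9 does not close the gap when Visit 17 is itself the last visit.

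**Conclusion.** The protocol is inconsistent as written. Sections 7.5.6 and 7.3.4 identify the 3-month point with a visit that section 7.1.2 and Appendix 1 allow between days 70 and 98. The visit can precede the 3-month point by at most 14 days on a 12-week reading, with no shortfall at target. On a calendar-month reading it can precede it by at most 19 to 22 days, with 5 to 8 days at target. These figures rest on an assumption about the length of 3 months, because the protocol gives none.

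Contraception would end early only where staff take the visit as the end point, and a pregnancy within the period would miss scheduled testing only in a woman with an early Visit 17 and no Visit 18. The documents do not allow the number of such women to be estimated. Separately, the sections conflict on the last pregnancy test whenever Visit 18 is held.

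Severity is minor. No endpoint, sample size, alpha level or treatment comparison is affected. It still merits correction because the text is an operative participant-safety rule.

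**What to change.** Reconcile sections 7.5.6, 7.3.4 and 7.5.4 with section 7.1.2, criterion 9 of section 4.1, Appendix 1 and Appendix 2. There are two ways to do so:

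- state the end of the contraception period by date, counted from the last vaccination, and delete the words in section 7.5.6 that equate it with Visit 17, with the matching change in section 7.3.4; or
- align Visit 17 and its window with the period as stated.

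In either case, name the last pregnancy-test visit in the same way in sections 7.3.4, 7.5.4 and 7.5.6 and in Appendix 2, for participants with and without Visit 18, and say what 3 months means in days. The length of the period, and which of the conflicting statements should govern, are for the sponsor to decide.

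The first option costs a wording amendment to the protocol and, where the same wording is used, to the information sheets. The second also changes a visit date or window, so Appendices 1 and 2 would need to follow. Neither needs an additional scheduled visit if the test is tied to an existing or unscheduled contact.

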### **7.5.7 Serious adverse events**

A serious adverse event is defined in **section 8**.

All serious adverse events should be reviewed by the Principal Investigator for the clinical centre, and discussed at the next Trial Management Group call.

A serious adverse event might cause a PI to consider discontinuing dosing or withdrawing a participant from the trial.

For all serious adverse events, the investigator will complete a serious adverse event CRF and report it to Monitors, TMG, Sponsor and DSMB, within 24 hours of learning of the event as described in **section 8.2**, and on to the ethical committees and regulatory authorities in the timelines required by each authority.

### **7.5.8 Other adverse events**

Any other systemic or local events which are not listed as solicited within the 7 days post immunisation observation, or which are listed but occur after the 7 days post immunisation observation period will be regarded as an adverse event and need to be recorded in the Adverse Events CRF. These will be recorded as reported following an open question to volunteers, with the dates of commencement and resolution, the outcome at the end of the study, required treatment, relationship to the study agent and potential effects on the vaccination schedule. Where a diagnosis is possible, it is preferable to report this rather than a series of terms relating to the diagnosis. When reporting a syndrome, the associated signs and symptoms will be indicated in the comment section of the CRF following the syndrome rather than as separate events. All grade 3 or 4 adverse events or serious events and/or those that necessitate a physician's visit or are treated with a prescribed medication will be evaluated. The participants will be followed carefully until the condition is resolved and/or the cause is identified. Any medication or other therapeutic measure taken to relieve symptoms of the medical problem must be recorded on the appropriate case report form.

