### 6.2 Administration of vaccines

The immunizations will take place in an outpatient setting. Prior to each immunization participants will receive a baseline medical status check up including vital signs assessment to confirm the medical eligibility before vaccine administration. Safety lab procedures, urine analysis as well as HIV testing will be performed before vaccine administration. A pregnancy test for female participants will have to show negative results before each immunization.

The study pharmacist will draw the vaccines or placebos into the applicable syringes for the Zetajet devices in case of DNA vaccinations or into syringes for IM use in the case of the MVA and CN54 rgp140/GLA-AF vaccinations according to standardized operational procedures. Prior to use the vials will be thawed at room temperature. Thawed vials will then gently be swirled. Care will be taken not to shake or invert the vials.

Upon receipt of the syringes the study nurse/study doctor will deliver the vaccine.

The DNA vaccines/placebo will be administered in one or two injections ID using the needle free Zetajet® device at weeks 0, 4 and 12. The prepared syringes will be loaded into the Zetajet by the study pharmacist according to manufacturer's instructions. The Zetajet will be applied on the disinfected skin with light pressure. The study agent is expelled under pressure through a micro-orifice at high velocity in a fraction of a second. The study product should be administered as soon as possible after preparation. If this is not possible, the syringe may be stored under refrigeration (2 to 8°C) but the product must be administered within 4 hours after being drawn up into the syringe.

For study groups II and III electroporation using the Derma Vax™ device will be applied immediately after immunization over the injection site according to manufacturer's instructions and SOP. The Derma Vax™ DNA Electroporation System is a device that delivers a tightly controlled and documented series of electrical pulses to the skin between two arrays of 2 mm long needles 4mm apart.

The CMDR-MVA vaccine/placebo boosting will be administered IM using suitable needles and syringes at weeks 24 and 40 into the deltoid muscle of the left arm. The MVA will be given in a dose of  $10^8$  pfu infectious doses in 1 ml volumes (groups IA, IIA, IIIA) or 1 ml sterile saline will be injected (groups IB, IIB, IIIB).

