##### 9.2.1.2 Safety

The primary **safety** endpoint is a grade 3 or above local or systemic clinical and laboratory solicited adverse event (see **section 7, Table 2**) or any grade of adverse event that results in a clinical decision to discontinue further immunisations.

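### The 7-day rule for solicited events conflicts with the laboratory schedule, so it is unclear which grade 3 or above laboratory results count in the primary safety endpoint

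*Protocol*

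**What the plan says.** **Endpoint.** Section 9.2.1.2 defines the primary safety endpoint as a "grade 3 or above local or systemic clinical and laboratory solicited adverse event", with a reference to Table 2, or "any grade of adverse event that results in a clinical decision to discontinue further immunisations". Neither part has a time window. Section 9.5.3 compares the groups on this endpoint with Fisher's exact test.

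**Laboratory events are solicited events.** Section 7.5.5 says of solicited events: "These include disturbances in routine laboratory parameters". Table 2 lists the parameters in a row labelled as systemic laboratory events: "Creatinine, ALT, total and direct bilirubin, glucose", followed by haemoglobin, white cells, neutrophils, lymphocytes and platelets.

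**The 7-day rule.** Under Table 2, events of the listed kinds that start within 7 days of a dose are taken to be at least possibly related. The text continues: "If the onset of the event is beyond 7 days, the event will be recorded on the adverse event CRF", and the investigator then decides on relationship. Section 7.5.8 speaks of local or systemic events that are not listed "or which are listed but occur after the 7 days post immunisation observation period will be regarded as an adverse event".

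**The laboratory route.** Section 7.5.5 adds that systemic laboratory events are collected by routine testing on the Appendix 2 schedule. Section 7.2.3 also refers to solicited laboratory values. Neither statement sets a time limit.

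**Timing of blood.** Section 6.2: "Safety lab procedures, urine analysis as well as HIV testing will be performed before vaccine administration". Section 7.1.2 and Appendix 1 place the first visit after each dose at 14 days, ±3. A later paragraph of 7.1.2 gives the 2-week visit after the second MVA a window of ±7 days. Section 7.1 allows safety blood at unscheduled visits when clinically indicated.

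**The concern.** A 7-day window suits diary-card symptoms. It does not suit laboratory values that are first looked at two weeks after a dose. If the window also governs the laboratory rows of Table 2, a confirmed grade 3 neutropenia first found at Visit 12 and dated to that visit becomes an ordinary adverse event. It would then fall under the any-grade secondary outcome (9.2.2.2). If the schedule governs, the same result belongs to the primary endpoint. The Protocol does not say which rule prevails.

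At stake is what is counted in a primary between-group comparison. With few grade 3 events, including or excluding the laboratory ones could change the result. The rule also affects site practice during the trial, because it decides which form an event goes on and whether relationship is presumed or judged. Section 7.6 notes that this is the first time MVA-CMDR and CN54rgp140/GLA-AF are given at the same timepoint, so a clear laboratory endpoint has practical value.

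**Working it through.** The Protocol gives no figure to reproduce here. The check is date arithmetic on Appendices 1 and 2.

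**Inputs.** Dose days: 0, 28, 84, 168, 280 (Visits 3, 5, 8, 11, 14). Haematology and chemistry after enrolment: Visits 4 to 18, which is 15 draws.

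**Formula.** Days since last dose = target day of draw − day of the most recent earlier dose. A dose-day draw is taken before that day's dose, so it is measured from the previous one.

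| Draws | Days since last dose |
|---|---|
| First after each dose: V4, V6, V9, V12, V15 | 14−0, 42−28, 98−84, 182−168, 294−280 = 14 each |
| Pre-dose on dose days: V5, V8, V11, V14 | 28−0 = 28; 84−28 = 56; 168−84 = 84; 280−168 = 112 |
| Second safety visit: V7, V10, V13, V16 | 56−28, 112−84, 196−168, 308−280 = 28 each |
| Long-term: V17, V18 | 364−280 = 84; 448−280 = 168 |

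**Result.** The smallest target interval is 14 days, so 0 of 15 scheduled draws, following 0 of 5 doses, are targeted within 7 days after a dose.

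**Windows.** With ±3 days the earliest compliant draw is 14 − 3 = day 11. With the competing ±7 days it is 14 − 7 = day 7, for Visit 15 only. So 1 of 5 doses could just reach the edge of the 7-day period.

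**The two readings of a confirmed grade 3 value found at a scheduled visit.**
- Under the Table 2 note and 7.5.8, the value is not solicited if its onset or occurrence is dated to the visit. Visit 15 drawn exactly on day 7 is the only scheduled exception.
- Under the laboratory sentence of 7.5.5, with 7.2.3 and 9.2.1.2, the value is a solicited laboratory event and counts at any scheduled visit.

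**How many events might be affected.** The documents support no useful estimate. Section 2.3 reports one grade 3 neutropenia among 40 TaMoVac I participants given CN54rgp140/GLA-AF, judged probably not related. The rate 1/40 = 2.5% has an exact 95% interval of about 0.06% to 13%. For the 90 participants planned for the protein boost this gives 90 × 0.025 = 2.25 events, with a range of about 0.06 to 12. Section 2.3 also does not say on which day the event was found.

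**The case against.** A reader might infer that the laboratory part of the endpoint can never be met. The documents do not support that.
- The laboratory sentence in 7.5.5 is the more specific one and carries no 7-day limit, so it can be read as the rule for laboratory events.
- Section 7.5.8 says its events are recorded after an open question to volunteers. That fits symptoms and not a creatinine or neutrophil value.
- The wider window lets Visit 15 reach day 7, and unscheduled blood may be taken earlier if clinically indicated.
- The Table 2 note turns on onset. An abnormality first seen on days 11 to 17 may have begun within 7 days.
- A laboratory event that leads to discontinuation counts at any time under the second part of the endpoint.

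A reader might also infer that the choice will be made after the laboratory data are known, or that laboratory toxicity would vanish from the report. Neither follows. Sections 9.5 and 9.5.2 place the statistical analysis plan before the main analysis, and it could fix the window. Any-grade events remain a secondary outcome, 9.5.3 reports safety by group and time-point, and the values stay on the laboratory reports.

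These points rule out the strong reading and make the scheduled-laboratory reading plausible, perhaps the intended one. They do not remove the conflict. The note under Table 2 covers all the listed events, and 7.5.8 covers systemic events, which is how Table 2 labels the laboratory rows. Neither makes an exception. Onset does not settle the matter either: the onset of a symptomless abnormality found on day 14 is not observed, so its classification would rest on assumption. An analysis plan could rebuild the counts from laboratory reports, but it could not make relationship assessments consistent if sites had followed different rules.

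**Conclusion.** The point holds as an inconsistency in the definition of the primary safety endpoint. Two stated rules disagree on whether a laboratory result found after day 7 is solicited, and every scheduled post-dose draw is targeted after day 7 (day 14 at the earliest). Depending on the rule followed, the endpoint takes in almost none of the scheduled grade 3 or above laboratory results, or all of them.

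This rests on reading the Table 2 note and 7.5.8 as they are worded, and on dating an abnormality to the visit at which it is found. How many events would move between the primary and secondary outcomes is unknown. The single earlier neutropenia is too little to say, and no conclusion here depends on it. The matter is more than detail left to the analysis plan, because the Protocol itself states both rules and sites act on them.

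**What to change.** Reconcile the sections by wording. In 7.5.5, 7.5.8 and 9.2.1.2, state that the 7-day window applies only to local and systemic clinical solicited events. State also that the laboratory component counts any Table 2 parameter at grade 3 or above, confirmed on the repeat test that 7.2.3 already requires within 48 hours, at any scheduled or unscheduled draw after the first dose. Fix the end of the laboratory window before unblinding.

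Two refinements are optional and are not needed to resolve the conflict. One is to require a grade worse than the one before the first dose. The other is to end the window at the 4-week visit after the last dose, which would leave Visits 17 and 18 out of the endpoint.

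The cost is a wording change and a note to sites on which form to use. No visits or blood draws are added. The downside is that the reported primary safety rate may be slightly less favourable.
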